### Methods in analysis to handle protocol non-adherence and any statistical methods to handle missing data {20c}

By using a random effects mixed model, all participants with at least one valid measurement will be included in the analysis. Hence, intermittent missing is not expected to substantially bias the results. To address possible informative drop-outs, a sensitivity analysis will be performed using multiple imputation, including all available information on background characteristics and outcome. Random effects mixed model analysis will be used to handle data missing at random for any of the two follow-ups [37].

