### Sample size {14}

The sample size was calculated using data from a mHealth intervention pilot study (15 participants) [25]. To facilitate the application of the concept minimal clinically important difference (MCID), the sample size was calculated based on results for daily step counts rather than for total sitting time for which MCID has not been established in previous research. Based on an increase of 1496 (standard deviation = 2930) steps/day after 3 months, and incorporating a dropout rate of 15%, a total of 142 participants would have 80% power in finding a statistically significant difference in step count between the groups. Approximately 1500 steps/day can be translated to additional 15–25 min of daily walking (depending on walking speed) which we deem to be a minimal clinically important difference for physically inactive T2DM patients [32].

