## Statistical methods

### Statistical methods for primary and secondary outcomes {20a}

Random effects mixed model analysis will be used to determine changes between the two study arms. The threshold for statistical significance will be set at *p* < 0.05. To avoid overestimating the impact of the intervention, an intention-to-treat approach will be adopted to evaluate the impact on the primary and secondary outcomes.

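### The multiple imputation offered against informative drop-out assumes missing at random as described, so its agreement with the mixed model would not show robustness to informative drop-out

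*Protocol article*

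**What the plan says.** The protocol article's section on non-adherence and missing data (item 20c) makes three statements.

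- On who is analysed: "By using a random effects mixed model, all participants with at least one valid measurement will be included in the analysis".
- On the sensitivity analysis: "To address possible informative drop-outs, a sensitivity analysis will be performed using multiple imputation, including all available information on background characteristics and outcome".
- On the assumption behind the main model: "Random effects mixed model analysis will be used to handle data missing at random for any of the two follow-ups".

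The section on statistical methods (item 20a) gives the aim that these choices serve: "To avoid overestimating the impact of the intervention, an intention-to-treat approach will be adopted".

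The article mentions no shift of imputed values, reference-based rule, pattern-mixture model, selection model or tipping-point analysis.

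**The concern.** Drop-out is informative when, after allowing for everything observed, it still depends on values that were not seen. The section contrasts two tools: the mixed model for data missing at random, and multiple imputation for informative drop-out. Yet the imputation is described only by its ingredients, "including all available information on background characteristics and outcome". Drawing missing values from a distribution fitted to observed data is valid under missing at random, which is the assumption the mixed model already makes. The stated purpose and the stated method do not match.

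What is at stake is how the sensitivity result would be read. If both analyses agree, the wording invites the conclusion that informative drop-out has been examined and found harmless, when it has not been examined. The question is a live one in this trial. It is open-label and behavioural, activity is measured by a thigh-worn accelerometer over seven full days at each visit, follow-up lasts 12 months, 15% loss is planned for, and the authors themselves raise informative drop-out.

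**Working it through.** **Inputs.** From the sample size section (item 14): "Based on an increase of 1496 (standard deviation = 2930) steps/day after 3 months", 15% drop-out, 80% power, 142 participants. From item 20a: significance at 0.05, taken here as two-sided. Allocation is 1:1. The article gives no standard deviation for total sitting time and no correlation between visits. The arithmetic is therefore on the step scale, and the correlation below is an assumption.

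**1. The plan's own figure.** Per arm, n = 2 × (1.96 + 0.84)² × 2930² / 1496², which rounds up to 61. Allowing for 15% loss gives 61/0.85, i.e. 72 per arm (144 in total), or 61 × 1.15, i.e. 71 per arm (142 in total). The stated 142 is reproduced, so 1496 and 2930 can serve as planning values.

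**2. Can the described imputation detect informative drop-out?** A large-sample simulation used 400,000 participants, three visits and a true 12-month difference of 1496 steps/day. Assumptions: correlation 0.6 between visits, 15% overall drop-out at 12 months, and log-odds of drop-out changing by 1.5 per standard deviation. The likelihood estimate and the imputation used the same step data, with no auxiliary variables.

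| Drop-out depends on | Likelihood | Imputation | Bias |
|---|---|---|---|
| Observed 3-month value | 1500 | 1499 | none of note |
| Unseen 12-month value, intervention arm only | 1862 | 1862 | about +366 (24%) |
| Unseen 12-month value, both arms | 1350 | 1349 | about −147 (10%) |

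The two analyses agree to within 1 step/day whether both are right or both are wrong. With the same variables in each, this is what theory predicts.

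**3. One illustration of size.** Suppose all intervention-arm drop-outs had no benefit and nothing in their observed data showed it. The missing-at-random estimate is 1496. The difference over everyone randomised is 1496 − 0.15 × 1496 = 1496 − 224 = 1272. The overstatement is 224/1272 = 18%.

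**4. What a controlled analysis would show.** Lowering imputed intervention-arm values by c steps/day changes the estimate by −0.15 × c:

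- c = 500 gives 1421
- c = 1000 gives 1346
- c = 1496 gives 1272
- c = 2930 gives 1057

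Completers per arm are 142 × 0.85 / 2 ≈ 60. The standard error is 2930 × √(2/60.35) ≈ 533, and significance is lost below 1.96 × 533 ≈ 1045. The tipping point is (1496 − 1045)/0.15 ≈ 3000 steps/day, ignoring the extra variance from imputation. For another observed difference d with the same standard error, it is (d − 1045)/0.15, so a smaller effect tips sooner. Imputation as described corresponds to c = 0 only.

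**The case against.** **The imputation rule is not spelled out.** Multiple imputation is also the vehicle for delta-adjusted and reference-based analyses, and a statistical analysis plan that is not shown may specify one. This stands as a limit: missing at random is inferred from the description, not declared. It does not remove the point, because the article itself pairs a purpose with a description that does not meet it.

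**A reader might infer that the imputation is redundant and must repeat the main result.** The article does not support that. It records occupation, working hours, complications, other chronic disease, fatigue, pain, self-efficacy and diet, any of which may be absent from the mixed model. If drop-out is related to such variables, the imputation can differ from the mixed model and correct it. The simulation had no auxiliary variables, so its close agreement does not carry over to that case.

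**A reader might infer that the benefit will be overstated.** That does not follow either. Both arms have the same visits, the same accelerometer week and nurse counselling. Nothing in the article shows that people who stop responding to the tracker or messages are the ones who leave. With outcome-dependent drop-out in both arms, the simulated bias was downwards.

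**The 18% is one scenario.** It needs every intervention-arm drop-out to have had no benefit and to have shown no sign of it. Someone who had faded by 3 months and then left would be imputed partly from that observed value. At the planning values, 1272 is still above 1045, so significance would not be lost. All of this stands.

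**Conclusion.** The mismatch is real. As described, the sensitivity analysis makes the same missing-at-random assumption as the main model. It can address drop-out explained by measured characteristics, but not drop-out that depends on unseen outcomes. Agreement between the two would therefore not support a claim of robustness to informative drop-out.

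Neither the size nor the direction of any bias can be settled from the article. Under the assumed mechanisms it ran from about −147 to about +366 steps/day, and the simple no-benefit scenario gives 224. These figures rest on the planning effect and standard deviation, 15% drop-out, and an assumed correlation and drop-out model. They concern steps, and no equivalent can be worked out for total sitting time.

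It would go too far to conclude that the main analysis is invalid. The mixed model, the intention-to-treat approach and the sample size are untouched. This is a should-fix matter about a sensitivity analysis and how it may be interpreted.

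**What to change.** - Keep the mixed model as the main analysis.
- Keep the multiple imputation, but call it a missing-at-random check with auxiliary variables and list those variables. Drop the claim that it addresses informative drop-out.
- Add a pre-specified analysis that departs from missing at random, for both total sitting time and steps. Use reference-based imputation for missing intervention-arm values at 3 and 12 months, a delta-adjusted tipping-point analysis, or both.
- Vary the delta shifts separately by arm, since the bias could go either way, and report where significance is lost. The range must be wide enough to get there. A range ending at the planning effect of 1496 steps/day would stop short, because the tipping point at planning values is about 3000. Set the range for sitting time in minutes on its own scale.

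The cost is a few sentences and modest programming, with no change to data collection or sample size. The sensitivity estimate may be less favourable than the main one. The change is best made before outcome data are analysed.

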### Plans to give access to the full protocol, participant-level data and statistical code {31c}

There are no plans for granting public access to the full protocol, participant-level data and statistical code.

### Composition of the data monitoring committee, its role and reporting structure {21a}

Research coordinators at the clinical research centre at Umeå University/Region Västerbotten and the principal coordinating investigator will regularly monitor data that is entered in REDCap. The clinical research centre is independent from the sponsor and has no competing interests.

### Adverse event reporting and harms {22}

The regional coordinating investigator will be notified by study personnel in case of an adverse event. All adverse events will be reported in REDCap.

### Frequency and plans for auditing trial conduct {23}

Not applicable. There is no on-site auditing of the trial.

### Plans for communicating important protocol amendments to relevant parties (e.g. trial participants, ethical committees) {25}

The trial steering committee will communicate substantial protocol modifications (when applicable) to relevant parties (referral Ethics Committee, trial participants and study personnel).

## Dissemination plans {31a}

Results of the trial will be published in international peer-reviewed scientific journals. There is no obligation for communicating the results to individual patients.

## Discussion

The ROSEBUD study will evaluate whether mHealth (activity tracker and SMS text reminders), in addition to counselling and telephone follow-up by a diabetes specialist nurse, will lead to reduced sitting time and increased steps. In addition, the ROSEBUD study will contribute to an increased understanding of the long-term health impact of occupational sedentary behaviour in adults with T2DM. If effective, this intervention could be implemented within typical primary health care settings and integrated in regular diabetes specialist nurse check-ups.

The modern office workplace is conducive to workers spending large amounts of time sitting [31]. Prolonged sitting time has emerged as a significant health concern which makes the workplace an important target for intervention [38]. The health benefits of more movement and less sedentary time are now well recognized. Indeed, the recent WHO guidelines now also promote reductions in sitting time [39]. However, research on the health effects of breaks in prolonged sitting time in people with chronic conditions like T2DM is still limited [40, 41]. Also, increasing movement at work may be more challenging for people with obesity and T2DM [42]. Nevertheless, previous research suggests that interventions using a variety of strategies are more likely to succeed [5, 32]. Accordingly, interventional strategies that include education on sedentary behaviour, motivational support and environmental cues (i.e. sit-stand desks) may facilitate reduced sitting at work [5, 11, 32]. mHealth technologies, including SMS text reminders and activity trackers, seem to support the individual behaviour change in individuals with T2DM and could therefore be valuable for individualized feedback in several different workplaces [25]. In addition, several wrist-worn activity trackers are programmed to prompt the users to reduce prolonged bouts of uninterrupted sitting [21].

Among those with T2DM, prolonged, uninterrupted sitting increases fatigue compared to interrupted sitting by regular brief activity breaks [4]. A reduction in prolonged occupational sitting may not only reduce fatigue and increase health-related quality of life but may also limit the number of sick days and improve work productivity [43]. Few trials evaluated interventions that reduce occupational sitting time among employees with chronic diseases. The ‘Stand and Move at Work’ multicomponent workplace intervention study tested the effects on health parameters of sit-stand workstations among 630 full-time employees of which 95 participants had prediabetes or diabetes [16]. Among the subgroup with prediabetes and diabetes, even small improvements in physical activity and sedentary time might be associated with a clinically meaningful decrease in cardiovascular risk [16]. A systematic review and meta-analysis found that interventions targeting sedentary behaviour reductions (alone or combined with increases in PA) are effective in decreasing cardiometabolic risk to a small degree but there is still paucity of evidence on long-term interventions in populations with chronic diseases such as T2DM [17].

In conclusion, a cost-effective, pragmatic intervention is needed to reduce the detrimental effects of prolonged uninterrupted sitting among individuals with T2DM. However, long-term trials are limited. Simple and easy-to-use activity trackers and SMS text messages are often inexpensive and therefore realistic to be utilized in primary health care settings. The ROSEBUD study will provide more clarity on the long-term health effects of a mHealth intervention for reduced sitting time in people with T2DM. Further, this study will provide clinically important knowledge that may improve diabetes management.

## Trial status

The first participant was recruited on the 14th of December 2020. The recruitment process is planned to be completed approximately on the 31st of December 2022.

## Data Availability

The first and the last author as well as the monitoring committee of the clinical research centre at Umeå University/Region Västerbotten have access to the final trial dataset.

## Abbreviations

T2DM: Type 2 diabetes mellitus
mHealth: Mobile health technology
PA: Physical activity
RCT: Randomized controlled trial
ADA: American Diabetes Association
GOe: The Global Observatory for eHealth
SMS: Short Message System
ROSEBUD: Reduced Occupational SEdentary BehavioUr in type 2 Diabetes
REDCap: Research Electronic Data Capture
eCRF: Electronic Case Report Forms
BMI: Body mass index
HbA1c: Haemoglobin A1c
MFI-20: The Multidimensional Fatigue Inventory-20
GSE-10: General Self-Efficacy scale
